### Interventions

#### The experimental intervention

Patients randomized to three years of extended SEI service continue to have access to the entire package of SEI services for an additional three years, following the initial two years of SEI. The following services, offered at the main PEPP site, constitute the experimental intervention:*Modified assertive case management* will continue to be one of the core treatment services provided. The case manager, with professional backgrounds primarily in social work or nursing, who has been involved in the patient’s care in the first two years, continues to provide the same service. This includes supporting the patient towards the attainment of appropriate treatment goals with a moderate case manager to patient ratio (20:1). Goals of treatment typically emphasize adherence to antipsychotic medication, reintegration into employment and/or educational activities, improving patients’ understanding about their illness, reducing dependence on hospital services, providing crisis intervention, promoting independence, monitoring early signs of relapse and reducing the risk of being engulfed by the illness. A personalized profile of the patients’ early warning signs [34,35] is created jointly in collaboration with the patient and used as a tool for the patient and the case manager to monitor any symptoms that might signal future relapse. Case management is provided as per the patients’ needs, using a guideline of a minimum of two contacts per month.*Multiple Family Intervention* is offered to the patient’s family as booster sessions of structured family education intervention and multiple family group intervention [36] similar to what is offered during the first two years.*Psychoeducation for families* is offered once a year and as booster sessions to the patient’s family. Workshops are designed as three two-hour sessions where families can ask questions and learn about psychosis, treatment and support.*Cognitive behaviour therapy* (*CBT*), known to be highly effective for those with psychosis [37,38], is offered in the case of a major depressive episode, anxiety disorder or residual psychotic and/or negative symptoms.*Substance abuse education and monitoring* for problems associated with substance abuse is offered to patients who, at initial presentation had a co-morbid diagnosis of substance abuse or developed substance abuse during the first two years of treatment. Therapists have received training to provide a brief (one-two sessions of 40–60 minutes each) intervention based on Motivational Interviewing [39]. The administration of the Timeline Follow-Back procedure followed by feedback [40] is used to help patients track their own alcohol and drug consumption. Patients are referred to appropriate rehabilitation if needed.

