**Methods:**

Following an initial 2 years of SEI, patients are randomized to receive either 3-years of continued SEI or regular care. SEI provided at three sites within the McGill network of SEI services, using a model of treatment comprised of: modified assertive case management; psycho education for families; multiple family intervention; cognitive behavioural therapy; and substance abuse treatment and monitoring. Blinded research assistants conduct ongoing evaluation of the outcome variables every three months. The primary outcome measure is remission status measured both as the proportion of patients in complete remission and the mean length of remission achieved following randomization during the additional three years of follow up. Based on preliminary data, it is determined that a total of 212 patients are needed to achieve adequate statistical power. Intent to treat with the last observation carried forward will be the primary method of statistical analysis.

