**Diagram of study participants in PEPP trial of extended SEI.**

### Recruitment

Patients who have received ongoing modified case management for the entire two-year period are screened for their participation. Patients that meet the inclusion criteria are approached for their participation between months 21 and 24 of SEI from one of the three McGill network SEI sites. The principal site of recruitment is the Prevention and Early Intervention Program for Psychosis (PEPP-Montreal), established in 2003 and the largest of the three sites; FEP Program at the Jewish General Hospital (established in 2007) and the PEPP at the McGill University Health Centre (established in 2009).

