
#### The control intervention

Patients randomized to the control condition receive treatment as usual in general medical or regular psychiatric services that are available for free to all Quebec patients. Primary regular care in Quebec is predominantly offered through local health and community services centres (CLSCs) that provide health and social services to their catchment area. Care by a family physician in the community is provided in a variety of settings, including at CLSCs and private clinics, and is of variable quality and intensity. Secondary (psychiatric) regular care, including hospital in- and out-patient services, offer a range of psychosocial rehabilitation services, that are part of regular care available to all patients randomized to the control condition.

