### Statistical analyses

Data analysis is based on the intent to treat principle. All patient evaluations will be included in the analysis. To assess homogeneity at baseline, relevant demographic data will be presented.

For the primary outcome measures, the proportion of patients in remission in the experimental and control groups will be compared using a Pearson chi-square statistic and the mean length of remission with a t-test or Wilcoxon test for independent samples, based on the distribution of the independent variable. Logistic regression analyses and multiple regression analyses will also be performed with all covariates and mediators.

For the secondary outcome measures including relapse (relapse vs. no relapse), dichotomous outcomes will be analyzed using logistic regression with covariates. Time to Event (relapse) will be measured using a Kaplan-Meier methods and Cox regression to analyze intervals of time from randomization to relapse. Continuous outcomes that include clinical outcomes will be assessed using regression models with covariates and finally longitudinal data with repeated measurements will be analyzed using repeated measures of analysis of variance.

Missing data will be assessed to determine if they are random or informative. Should missing data be non ignorable, then selection models and pattern-mixture models will be used to evaluate the robustness of the primary analyses.

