## Discussion

This study is based on previous data that suggests that the benefits of SEI services in FEP at two years are lost at five-year follow up if patients return to regular care [31]. Given the severity of psychosis and the individual and societal costs associated with this disorder, there is a need for research that can better guide best practices. That FEP patients are young and potentially still malleable to treatment, suggests the importance of positively influencing long-term trajectories of outcome. To our knowledge, this is the first RCT trial of its kind in North America, and one of only two such trials anywhere (OPUS-II) [61], being carried out currently to assess the impact of extended SEI for a total of five years in FEP. Several strengths of this study include the number of participants recruited as well as the computerized randomization procedure that ensures chance allocation to group. That we have included FEP patients with comorbid disorders, including comorbid substance use, and that patients in our control condition are likely to be filtered through a wide range of 1st, 2nd, and 3rd line services available, gives critical construct validity to our study. Given that the majority of service is provided out of a single site (PEPP-Montreal) with two satellite clinics that are closely aligned and that follow the same treatment system, homogeneity of service infrastructure and fidelity to the same SEI model of care is ensured. As well, we are measuring a host of critical variables that may give meaning to the context of remission. Variables including social and occupational functioning and negative symptoms at baseline have been shown to impact long-term trajectories in FEP [12,13]. Measures of quality of life bring into focus the personal perspectives of this disorder while concurrent measures of all associated economic costs will highlight societal burden. This trial is registered http://www.isrctn.com/ (ISRCTN11889976), which helps to ensure complete reporting.

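### Continuing case managers cluster patients in the extended SEI arm only, but the primary tests assume independent patients, so the standard error may be too small if managers differ in effect after randomisation

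*Protocol article*

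**What the plan says.** The protocol article (The experimental intervention) keeps each SEI patient with the case manager "who has been involved in the patient’s care in the first two years, continues to provide the same service". The manager's work is described as "supporting the patient towards the attainment of appropriate treatment goals with a moderate case manager to patient ratio (20:1", with two contacts a month as the guideline minimum.

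Under The control intervention, patients leave that structure. Family-physician care there "is provided in a variety of settings, including at CLSCs and private clinics, and is of variable quality and intensity", and hospital in-patient and out-patient psychiatry is also available.

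Before randomisation both arms had the same kind of care (Recruitment): "Patients who have received ongoing modified case management for the entire two-year period are screened for their participation". Randomisation is by individual patient, stratified by sex and substance abuse, not by site or case manager.

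Statistical analyses names the primary tests: the remission proportions are to be "compared using a Pearson chi-square statistic and the mean length of remission with a t-test or Wilcoxon test for independent samples". Supplementary regressions refer to covariates and mediators without naming a provider term. Power and sample size mentions no ICC or design effect. The Discussion states that "homogeneity of service infrastructure and fidelity to the same SEI model of care is ensured", without a figure.

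**The concern.** After randomisation, SEI patients share case managers and control patients mostly do not share a provider in the same way. This is a partially nested design, clustered in one arm. If some managers get better results than others over the three years, two SEI patients with the same manager resemble each other more than two patients drawn at random, and the SEI arm holds less information than its head count suggests. A chi-square, t-test or Wilcoxon test does not see this.

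The protocol's own hypotheses make such differences plausible: working alliance with the treatment provider is expected to predict adherence and retention, and adherence to mediate remission. What is at stake is whether a significant result can be read as an effect of the SEI model in general, or partly reflects which clinicians delivered it.

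The point does not depend on what an unseen analysis plan may add. The article itself fixes independent-sample tests as the primary comparison.

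**Working it through.** **Step 1. Reproduce the planned sample size.** Inputs from Power and sample size: 41.8% and 69%, each moved by 5%; 80% power; 82 per group; dropout of 25% and just under 20%. Level and sidedness are not stated; two-sided 5% is assumed.

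Reading the 5% as relative: control 0.418 × 1.05 = 0.4389; SEI 0.69 × 0.95 = 0.6555; difference 0.2166; mean 0.5472.

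n = [1.96 √(2 × 0.5472 × 0.4528) + 0.84 √(0.4389 × 0.5611 + 0.6555 × 0.3445)]² / 0.2166² = (1.380 + 0.578)² / 0.0469 = 81.7, so 82 per group.

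Dropout: 82/0.75 + 82/0.80 = 211.8, so 212.

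Both stated figures reproduce as an independent-patients calculation. No allowance for clustering is built in.

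**Step 2. Inputs that have to be assumed.** Let m be the number of trial patients per manager. If caseloads of 20 held only SEI-arm trial patients, the 109 enrolled (Trial status) would need 109/20 = 5.45, so at least 6 managers, or about 18 each. That is an upper end. Caseloads may include patients outside the SEI arm, so m = 5 and m = 10 are also shown. The ICC is assumed to be 0.01 to 0.05; at zero nothing changes.

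**Step 3. Formulas.** Clustering is applied to the SEI arm only, with roughly equal arm variances.

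- Design effect: DE = 1 + (m − 1) × ICC
- True standard error over the one used: R = √((DE + 1)/2)
- True level of the planned test: 2 × [1 − Φ(1.96/R)]
- Power of a test correctly held at 5%: Φ(2.80/R − 1.96)
- Power of the planned, uncorrected test: Φ((2.80 − 1.96)/R)

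Here 2.80 = 1.96 + 0.84, the standardised difference giving 80% power at 82 per arm.

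**Step 4. Results.**

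| m | ICC | DE | R | True level | Power, corrected test | Power, planned test |
|---|---|---|---|---|---|---|
| 5 | 0.01 | 1.04 | 1.01 | 5.2% | 79% | 80% |
| 5 | 0.05 | 1.20 | 1.05 | 6.2% | 76% | 79% |
| 10 | 0.01 | 1.09 | 1.02 | 5.5% | 78% | 79% |
| 10 | 0.05 | 1.45 | 1.11 | 7.7% | 72% | 78% |
| 18 | 0.01 | 1.17 | 1.04 | 6.0% | 77% | 79% |
| 18 | 0.05 | 1.85 | 1.19 | 10.1% | 65% | 76% |

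**Step 5. Consistency of the worst row.** m = 18 comes from 109 enrolled, while the power figures use 82 per arm. Six managers sharing 82 patients gives m = 13.7. At ICC 0.05, DE = 1.63, R = 1.15, true level 8.8% and corrected power 68.5%. With all 109 retained and m = 18, the standardised difference is 2.80 × √(109/82) = 3.23; corrected power is Φ(3.23/1.19 − 1.96), about 77%, and planned-test power Φ((3.23 − 1.96)/1.19), about 86%. The 10% level and 65% power are therefore the pessimistic corner of the range.

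**The case against.** The strongest reply is that none of the three quantities that set the size is documented. A reader might infer from the 20:1 ratio that a handful of managers each treat about 20 trial patients. The article does not say so. The ratio is a service caseload, and the services also treat patients aged 14 to 17 and patients still in their first two years. With 5 trial patients per manager the level is only 5.2% to 6.2%. This stands, and it limits the size of the point.

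Second, patients are randomised individually. If the intervention changes no patient's outcome, randomisation keeps the level near 5% however outcomes cluster. Managers were also in place before randomisation, so effects already present are spread over both arms and largely cancel. Inflation needs real differences between managers that arise afterwards, and an inference meant to reach beyond these particular managers. This stands too. That wider inference is, however, the one the article wants, since it expects its results to guide the recommended duration of SEI services.

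Third, a reader might infer that the planned analysis has only 65% power. It does not. That figure belongs to a test corrected to hold 5%; over the same range the planned test keeps about 80% to 76%.

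Fourth, a reader might see a contradiction between "The following services, offered at the main PEPP site, constitute the experimental intervention" and "SEI provided at three sites within the McGill network of SEI services". The wording is unclear for patients from the two satellite clinics, but both statements can hold if those patients attend the main site, and the matter adds nothing to the claim about standard errors. The Discussion's assurance of homogeneity likewise neither proves nor disproves variation between managers.

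Finally, a mixed model with perhaps six clusters estimates the manager variance poorly. That is a reason to use it beside the planned tests and not in their place.

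What survives is the direction: any positive between-manager variance arising after randomisation makes the standard error in the named tests too small for inference beyond these managers.

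**Conclusion.** The concern holds in a conditional form. The article places continuing, shared case managers in the SEI arm only and fixes independent-sample tests for both primary outcomes, so the reported precision may be too high. Over the assumed range the effect runs from negligible (a standard error 1% too small in relative terms, at 5 trial patients per manager and ICC 0.01) to material (a true level near 10%, at 18 and 0.05). The documents do not show where in that range the trial lies, and they do not support saying that the intervals are definitely, or by any known amount, too narrow. The calculation rests on a normal approximation, a two-sided 5% level, the relative reading of the 5% adjustments, and no correlation among control patients.

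**What to change.** Keep the planned chi-square and the t-test or Wilcoxon test. Take case manager and site from clinical records for all 220 patients; for control patients this is the manager who held the case before randomisation. Table 1 does not list case manager, so its availability in the records should be confirmed.

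Prespecify, before outcomes are examined by arm, a partially nested mixed model as a sensitivity analysis of both primary outcomes: logistic for the remission proportion and linear for length of remission, with a random case-manager effect in the SEI arm, site as a fixed effect and a small-sample correction. Report the number of managers, the trial patients per manager and the estimated ICC. State in advance that the conclusion will be qualified if this analysis and the planned test disagree.

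The cost is analysis-plan wording and two variables extracted from records, with no new patients or visits. The downside is wider intervals and, with few managers, an imprecise variance estimate.

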
#### The control intervention

Patients randomized to the control condition receive treatment as usual in general medical or regular psychiatric services that are available for free to all Quebec patients. Primary regular care in Quebec is predominantly offered through local health and community services centres (CLSCs) that provide health and social services to their catchment area. Care by a family physician in the community is provided in a variety of settings, including at CLSCs and private clinics, and is of variable quality and intensity. Secondary (psychiatric) regular care, including hospital in- and out-patient services, offer a range of psychosocial rehabilitation services, that are part of regular care available to all patients randomized to the control condition.

### Assessments

Evaluations and assessments are carried out at entry and every three months thereafter for the entire follow up period, or until withdrawal from the study, for both treatment conditions (details of assessments are provided in Table 1). If a patient withdraws, they are asked to provide one last assessment. When no contact has been made for 3 consecutive assessment periods (for a total of 9 months) and attempts made for contact through phone calls, emails, and contact with care providers including family members, are not successful, the patient is considered to be withdrawn. Trained evaluators will conduct assessments largely through a semi structured interview format.

**Table 1 Tab1:** **Assessment instruments**

**Assessment**	**Instrument**
Psychopathology	Scale for the Assessment of Positive Symptoms (SAPS) [41]*
	Scale for the Assessment Negative Symptoms (SANS) [42]*
	Positive and Negative Syndrome Scale (PANSS) [43]*
	Brief Psychiatric Rating Scale (BPRS) [44]*
Functioning	Global Assessment of Functioning Scale (GAF) [45]*
	Social and Occupational Functioning Scale (SOFAS) [46]**
	Productivity Interview Questionnaire (adapted from the Client Socio-Demographic and Service Receipt Inventory) [47]*
	Life Skills Profile [48]**
Medication and side effects	Patient Compliance Interview [49]*
	Medication Compliance: Pill Count Form [49,50]*
Substance use	Chemical Use/Abuse/Dependence-Scale (CUAD) [51]*
	Time Line Follow Back [40]*
Working alliance	Working Alliance Inventory (WAI) [52]**
Randomization preference	Self administered questionnaire***
Quality of life	Life Satisfaction and Psychological Well-being domains of the Wisconsin Quality of Life-Client version [53]**
Duration of untreated psychosis	Circumstances of Onset and Relapse Schedule (CORS) [11]***
Promorbid adjustment	Premorbid Adjustment Scale (PAS) [52]***
Service use including hospital admittance and total bed days	Self administered questionnaire with list of services received
	Regie de l’Assurance-maladie du Quebec (Quebec medical insurance; RAMQ)****
	Med-Echo (for hospitalizations)****

*Assessed at each evaluation (every 3 months).

**Assessed at every second evaluation (every 6 months).

***Assessed once at baseline.

****Assessed post study completion.

Data on the Duration of Untreated Psychosis (DUP) are available for all PEPP patients and is derived using the Circumstances of Onset and Relapse Schedule (CORS) [11], a structured interview instrument for use with patients and families that includes some sections from the Interview for the Retrospective Assessment of Onset of Schizophrenia (IRAOS) [54]. DUP data for all other patients is available through chart verification.

### Outcomes

In light of more recent consensus criteria for remission that emphasizes the amelioration of positive as well as negative symptoms and a return to social and occupational functioning [55], a full range of complementary measures of clinical and functional outcome is being examined both separately and in context with each other.

### Primary outcome

The primary outcome is complete remission measured as both the proportion of patients in remission, as well as the mean length of remission achieved following randomization during the additional three years of follow up. Complete remission is defined according to consensus criteria as a rating of mild or less on the following positive and negative symptom scale items (Positive domain: hallucinations, delusions, bizarre behaviour, positive formal thought disorder; Negative domain: affective flattening or blunting; alogia; avolition-apathy; anhedonia-asociality) for a period of six months [55]. Complete remission is chosen as the primary outcome measure as per findings that remission across both symptom domains is a better predictor of functional outcome than remission of positive symptoms alone [56,57]. Remission is measured at each assessment covering the three months prior using the Scale for Assessment of Positive Symptoms [41] and the Scale for the Assessment of Negative Symptoms [42]. The SANS domain of Attention is not included in SANS ratings as these items have not been shown to correlate to the domain of negative symptoms [58].

### Secondary outcomes

*Clinical outcome*: (i) Relapse (defined as the reemergence of positive symptoms as measured by a global item on the SAPS of at least 3 in severity that leads to an increase or change in antipsychotic medication or to hospital admission) [59]; (ii) Level of positive and negative symptoms (SAPS [41] and SANS [42] ratings); (iii) Global Assessment of Functioning (GAF) [45]; (iv) Discontinuation of treatment as determined through a lack of service use.*Functional outcome* (assessed on two functional dimensions): (i) role functioning (paid employment, school attendance, and/or meaningful housework) and through; (ii) social functioning (such as independence in community living) assessed using the Life Skills Profile [48] as well as the Social and Occupational Functioning Scale (SOFAS) [46] as a global measure of functioning.*Quality of Life* (*QOL*): Subjective reporting of QOL is assessed at study entry and subsequently at every six months using the Life Satisfaction and Psychological Well-being domains of the Wisconsin Quality of Life-Client version [53].

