### Inclusion criteria

Our aim is to use inclusion criteria that are as non discriminatory as possible in order to ensure the ecological validity of this trial and to reflect the kinds of diverse patients seen in FEP clinical settings. Although the SEI services treat patients between 14 and 35 years old, for the purpose of the study, patients aged 18–35, with a DSM-IV diagnosis of a psychotic disorder (schizophrenia spectrum psychoses and affective psychosis), who have completed two years of SEI treatment and follow-up within the McGill network of SEI services, an IQ greater than 70, the ability to communicate in either French or English, and the ability to provide informed consent, are eligible for participation. Patients are recruited regardless of their remission status at the end of two years of SEI treatment, consistent with what may be seen in regular clinical practice. Ethics approval for this RCT was granted by McGill University’s Faculty of Medicine Institutional Review Board (Assurance number: FWA 00004545) and from the Douglas Hospital Research Ethics Board.

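### Relapse, defined as re-emergence that prompts treatment, is timed from randomisation in patients who may never have been free of symptoms, and its treatment clause depends on unblinded care that differs by arm

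*Protocol article*

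**What the plan says.** - **Event** (protocol article, Secondary outcomes). Relapse is "the reemergence of positive symptoms as measured by a global item on the SAPS of at least 3 in severity", and it must be one that "leads to an increase or change in antipsychotic medication or to hospital admission". Neither a preceding remission nor a preceding rating below 3 is spelled out.
- **Entry** (Inclusion criteria). "Patients are recruited regardless of their remission status at the end of two years of SEI treatment". The Randomization section stratifies by sex and substance abuse, not by remission.
- **Analysis** (Statistical analyses). "Data analysis is based on the intent to treat principle. All patient evaluations will be included in the analysis". Relapse is analysed twice: as a binary outcome ("relapse (relapse vs. no relapse), dichotomous outcomes will be analyzed using logistic regression with covariates") and as a time to event, by "Kaplan-Meier methods and Cox regression to analyze intervals of time from randomization to relapse". No at-risk subset is named.
- **Who decides** (Blinding; The experimental intervention; The control intervention). Clinicians are not blinded. SEI has a guideline of at least two contacts a month, and watching for early signs of relapse is part of it. Regular care has no stated minimum contact, and family-physician care is described as varying in quality and intensity.
- **Who rates symptoms** (Blinding; Assessments; Table 1). Blinded research staff rate the SAPS every three months in both arms.

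**The concern.** Two features of the endpoint do not fit the design.

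First, the word re-emergence presupposes that symptoms had gone. Entry regardless of remission and a clock that starts at randomisation put patients in the risk set who cannot yet have the event. If they are carried as at risk from day 0, or scored as relapsed at their first rating of 3 or more, they contribute little or nothing to the contrast between arms.

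Second, the symptom half of the event is rated blind on one schedule, but the other half is a medication change or an admission. Those decisions belong to unblinded clinicians, and the intensity of their contact is what the trial randomises. The same symptomatic return may therefore count in one arm and not in the other.

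A lower relapse rate is part of secondary hypothesis (c) in the Background. At stake is whether a difference in relapse, or the lack of one, can be read as a difference in illness course.

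**Working it through.** The article gives no relapse rate, no share symptomatic at entry and no power for relapse. Its sample-size figure of 82 per group concerns remission and does not bear on this point. Everything below illustrates assumed inputs.

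**Risk set.** Inputs: 111 control and 109 SEI patients (Trial status). Assumed: two-sided 5% test; three-year relapse of 45% vs 27% (control vs SEI) among patients at risk; 40% of each arm symptomatic at entry.

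Formula: power = Φ((|p0 − p1| − 1.96·SE0)/SE1), with SE0 = √[p̄(1 − p̄)(1/n0 + 1/n1)] and SE1 = √[p0(1 − p0)/n0 + p1(1 − p1)/n1].

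1. *At-risk subset.* n = 0.60 × 111 = 66.6 and 0.60 × 109 = 65.4; p̄ = 0.361; SE0 = 0.0836; SE1 = 0.0820. Power = Φ((0.18 − 0.1639)/0.0820) = Φ(0.20) = 58%.
2. *All 220, symptomatic patients never relapse.* 0.60 × 45% = 27% vs 0.60 × 27% = 16.2%. The difference is 10.8 points and power 49%.
3. *All 220, symptomatic patients counted as relapsed.* 27% + 40% = 67% vs 16.2% + 40% = 56.2%. The difference is again 10.8 points and power 38%.
4. *All 220, half of the symptomatic patients settle and then relapse at the same rates.* The share ever at risk is 0.60 + 0.40 × 0.5 = 0.80, giving 36% vs 21.6% and 66% power. With a quarter settling the share is 0.70, giving 31.5% vs 18.9% and about 58% power, level with the subset.

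Varying the share symptomatic at entry:

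| Symptomatic at entry | At-risk subset | All, never relapse | All, counted as relapsed |
|---|---|---|---|
| 20% | 70% | 66% | 57% |
| 40% | 58% | 49% | 38% |
| 60% | 42% | 33% | 23% |

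*Hazard-ratio scale.* A simulated Cox model (106 per arm for power, 20,000 per arm for the hazard ratio, three years, 50% vs 30% relapse, true hazard ratio 0.51) was run with 64% or 47% of patients at risk. The hazard ratio moved only to 0.54–0.57 when the others could not have an event. It moved to 0.68–0.77 when they had events at the control rate in both arms.

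**Treatment clause.** Observed relapse = true symptomatic return × share followed by a medication change or admission (capture).

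- Equal true return of 40%, capture 90% SEI and 70% control: 0.40 × 0.90 = 36% vs 0.40 × 0.70 = 28%, a false 8-point excess in SEI.
- True return 27% SEI and 45% control, same capture: 0.27 × 0.90 = 24.3% vs 0.45 × 0.70 = 31.5%. Power in 220 patients falls to 22%, from 80% with full capture and 73% with 90% capture in both arms.
- Capture reversed (70% SEI, 90% control): 0.27 × 0.70 = 18.9% vs 0.45 × 0.90 = 40.5%. The true 18-point benefit appears as 21.6 points.

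**The case against.** The case against has several parts that stand.

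- **Symptomatic patients can still relapse.** Over three years a patient may settle and then relapse, and the primary outcome itself counts remission reached after randomisation. A reader might infer that such patients should be dropped. The documents do not support that: once about a quarter of them settle, under the assumptions above, all 220 patients match the subset for power, and beyond that they do better.
- **The study baseline is not a safe basis for a subset.** The Blinding section places it in the first 3–6 weeks of randomisation, which reads as after it. The Randomization section has patients asked about their allocation and the treatment team told of it. A subset chosen on that SAPS rating could be affected by allocation.
- **The direction of the capture bias is unknown.** A reader might infer a bias against SEI, since closer contact gives more occasions to change treatment. But SEI clinicians may act on early signs before the SAPS reaches 3, so that less is counted. The remark on variable intensity also concerns family-physician care only; control patients can use psychiatric in- and out-patient services too.
- **Blinded symptom evidence already exists.** Remission is the primary outcome, and SAPS and SANS levels are secondary outcomes. This limits the damage, but neither is a relapse comparison.
- **Detail may sit in an analysis plan that is not shown.** That could cover how symptomatic entrants are counted. It does not remove the mismatch, because the article itself fixes the event, the entry rule and the time origin.

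**Conclusion.** The point holds in a limited form. As written, the relapse endpoint combines a re-emergence event, entry regardless of remission and a clock from randomisation without saying how patients at SAPS 3 or more at entry are counted. Holding them at risk from day 0, or scoring them as relapsed at once, reduces the absolute contrast and the power by an amount the documents do not allow one to compute. With 40% symptomatic, all-patient power runs from 38% to 66% depending on the counting rule and on how many settle, against 58% in the subset. The hazard ratio is little affected if these patients simply have no events.

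Separately, the treatment-or-admission clause makes the event depend on unblinded care that is monitored more closely in the SEI arm. Differential capture can create, hide or exaggerate a difference. The 90% and 70% capture rates are assumptions.

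Two stronger claims are not supported: that relapse is biased against SEI, and that a large share of patients is symptomatic at entry. The 41.8% and 69% remission figures under Power and sample size come from later follow-up in other studies. The primary outcome is not touched. The correction is worth making because it is cheap and relapse is a named secondary outcome.

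**What to change.** Record the following before any unblinded analysis.

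1. Add a relapse analysis whose event is a SAPS global of at least 3 at a blinded quarterly assessment, after an earlier rating below 3, without the treatment clause. Keep the published treatment-linked definition beside it, and draw a between-arm conclusion on relapse only where the two agree.
2. Keep all randomised patients in the intent-to-treat analysis, and state that symptoms persisting from entry are not counted as relapse.
3. Add an analysis restricted to patients below SAPS 3 at their last assessment before randomisation, or stratified by that status. Do not use the baseline taken 3–6 weeks after randomisation.

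**Cost.** No new visits or instruments, since the SAPS is already rated every three months. All 220 patients are already randomised, so this is a late addition and should be dated and reported as such. Event times will be known only to the quarter, and brief relapses between visits will be missed. The restricted analysis has fewer patients and needs symptom records from before randomisation, whose availability the article does not state. If one arm settles more of its symptomatic entrants, more of them also become able to relapse; the restricted analysis guards against misreading that.
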